### Protecting against sources of bias

#### Selection bias

Selection bias (such as bias-by-indication or survival bias) will be minimized through rigorous concealed randomization procedures. Although placebo controls have been used in some RCTs of antibiotic treatment duration, such as studies examining treatment duration for cellulitis [36], pyelonephritis [37,38], and community-acquired pneumonia [39-42], they are not appropriate for bacteremia treatment in the ICU. It will not be practical to provide placebos for each of the many antimicrobials commonly used alone or in combination to treat bacteremia due to varied infectious syndromes and pathogens; in our multicenter retrospective study more than 100 different species were identified in enrolment blood cultures, and more than 60 different individual antimicrobials were administered [43]. Even if it were feasible to generate this many placebos, patients in critical care may develop secondary sources of nosocomial infection, and clinicians will not agree to be unaware of whether their patients are already receiving active antimicrobial treatments versus placebo. The successful, landmark *PneumoA* trial of shorter versus longer duration treatment for ventilator associated pneumonia, did not employ placebos [19].

### Outcome misclassification bias

We have selected objective outcome measures, and we will use central adjudication committees blinded to treatment allocation for subjective outcomes including secondary infection or colonization with antibiotic resistant organisms [44,45].

### Publication bias

We will prevent publication bias by registering both the BALANCE Pilot Trial and the main BALANCE Trial, and through this publication of the trial protocol.

### Withdrawal from study

All consented patients will be followed regardless of adherence to the trial protocol. If a patient is withdrawn from the study prematurely, a withdrawal form will be completed. Data will be collected under the informed consent up to the point of a consent withdrawal. If permitted by the patient or substitute-decision maker, data collection will continue for withdrawn patients. Primary analyses will be carried out on the basis of *intention-to-treat* principle, safety outcomes will be assessed using per-protocol analyses. Anticipated reasons for withdrawal include patient not meeting inclusion criteria or relevant exclusion criteria present prior to randomization, consent withdrawn by patient or substitute-decision maker, patient’s physician believes patient should be withdrawn from the study, inadvertent duplicate randomization. Detailed rationales for withdrawal will be recorded.

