#### Exclusion criteria

Patient has severe immune system compromise, as defined by: absolute neutrophil count <0.5×10^9^/L; or is receiving immunosuppressive treatment for solid organ or bone marrow or stem cell transplant.Patient has a prosthetic valve or synthetic endovascular graft.Patient has a suspected or documented syndrome with well-defined requirement for prolonged treatment (infective endocarditis, osteomylitis/septic arthritis, undrainable/undrained abscess, or unremovable/unremoved prosthetic-associated infection).Patient has a single positive blood culture with a common contaminant organism according to the Clinical Laboratory & Standards Institute (CLSI) (coagulase negative staphylococci, *Bacillus spp., Corynebacterium spp., Propionobacterium spp., Aerococcus spp., Micrococcus spp*) [30].Patient has a positive blood culture with *Staphylococcus aureus* [31].Patient has a positive blood culture with *Candida spp.* or other fungal species as the only potential pathogen.Patient already or previously enrolled in the trial.

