### Trial interventions

We will randomize patients to receive a shorter duration of adequate antimicrobial therapy (7 days) versus a longer duration (14 days). Adequate antimicrobial treatment will be defined as a regimen with *in vitro* activity against the organism(s) responsible for the bloodstream infection; the duration of adequate treatment will be determined as the cumulative number of calendar days for which adequate treatment is delivered beyond the date of collection of the index blood culture specimen- the clock will start from initiation of the first adequate treatment dose after the blood culture has been drawn. The selection of specific antimicrobial agents, doses and route of delivery will initially be at the discretion of the treating clinical team. Most commonly the patient will already be receiving some empiric antibiotic treatment for suspected infection prior to the blood culture being documented as positive; the study protocol will not expose patients to potential antibiotic treatment delays. As soon as blood culture results are available (preliminary Gram staining), the research coordinator, in consultation with the site investigator and site infectious diseases co-investigator if necessary, will review the initial antibiotic choice to ensure adequate empiric coverage for the potential culprit organism(s). As blood culture results are finalized (speciation and sensitivity determination), they will re-review the antibiotic choice to ensure that the spectrum of activity is adequate. If the spectrum is inadequate, this will be communicated to the treating physicians. To avoid differentially influencing antibiotic choices and clinical decision-making, the randomization assignment will not be communicated to the study research coordinator, study critical care or infectious diseases investigators or clinicians until the end of day 7. The ICU research coordinator at each site will visit daily to ensure protocol adherence (antibiotics are stopped at the pre-specified date (end of the 7th or 14th day) and not earlier (Figure 1).

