### Frequency of analyses

The BALANCE Pilot Trial will be conducted and reported according to recommendations by the Consolidated Standards of Reporting Trials (CONSORT), including analyzing patients in the groups to which they were originally assigned (intention-to-treat) and explicit procedures for handling of any missing data [49].

Analyses will be conducted at the completion of this pilot, given that there is no role for early termination [50]. However, we will monitor recruitment and adherence rates weekly, and examine barriers as needed, working with participating centers to provide screening and consenting tips from prior CIHR-funded ICU trials [34]. Capturing a minimal dataset of patient, pathogen and bacteremia source characteristics among eligible nonenrolled patients will facilitate this, and comparisons with eligible patients will help to identify selection bias [49].

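### Withdrawal for ineligibility or by physician decision stays open after the arm is known, and the per-protocol safety analysis then drops patients judged ineligible

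*Protocol article*

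**What the plan says.** The protocol article, 'Withdrawal from study', opens with a broad commitment: "All consented patients will be followed regardless of adherence to the trial protocol". It says that data are gathered under the consent until consent is withdrawn, and then adds: "If permitted by the patient or substitute-decision maker, data collection will continue for withdrawn patients". The primary analyses are to follow intention-to-treat, but "safety outcomes will be assessed using per-protocol analyses".

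The same section lists the grounds for withdrawal. The first reads: "Anticipated reasons for withdrawal include patient not meeting inclusion criteria or relevant exclusion criteria present prior to randomization". Another is that the patient's "physician believes patient should be withdrawn from the study". The remaining two are withdrawal of consent and an inadvertent duplicate randomization. The rationale must be recorded. No time limit, evidence cut-off or blinded ruling is attached to any ground.

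Four other sections bear on this:

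- 'Exclusion criteria' includes: "Patient has a suspected or documented syndrome with well-defined requirement for prolonged treatment". Its examples are endocarditis, bone or joint infection, an undrained abscess and an infected prosthesis left in place.
- 'Trial interventions' withholds the assignment from the research coordinator and from "study critical care or infectious diseases investigators or clinicians until the end of day 7". Treatment is open after that.
- 'Subgroup analyses' defines the per-protocol set for safety as patients with perfect adherence, and names eligibility as one of the aspects.
- 'Frequency of analyses' commits to "analyzing patients in the groups to which they were originally assigned (intention-to-treat").

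**The concern.** Two of the withdrawal grounds rest on judgement, and both can be used after the treating team knows the arm. A deep focus of infection is often recognised only when a patient fails to improve. If one is found after day 7, someone must decide whether it was there before randomization and whether the patient was therefore ineligible. The condition in the first ground limits when the focus existed. It does not limit when, by whom, or on what evidence the decision is made.

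The arms are treated alike until day 7 and differ only afterwards, in the open. A decision made after day 7 can therefore depend on the arm, both through what has happened to the patient and through what the person deciding knows. Patients lost in this way would be late failures, which matter most in a comparison of durations. The pilot has no data safety and monitoring committee, and its patients may be carried into the non-inferiority main trial. The safety summaries from the pilot, and the data passed on, should not depend on such decisions.

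**Working it through.** The article gives no figure for withdrawals, so there is none to reproduce. The main check is of the text.

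**Step 1: is withdrawal possible once the arm is known?** Yes. The assignment is released at the end of day 7 and no ground for withdrawal has an end date. The blinded central committees under 'Outcome misclassification bias' are for subjective outcomes and are not given eligibility.

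**Step 2: does withdrawal end data collection?** This is unclear. Read in sequence, the permission sentence may apply only after consent has been withdrawn. But it speaks of withdrawn patients in general, and the section's list of withdrawals includes people who have not revoked consent. The opening commitment covers non-adherence and does not mention withdrawal.

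**Step 3: does withdrawal remove a patient from analysis?** For the primary analyses, no sentence says so, and the intention-to-treat statements point the other way. It is also not expressly said that patients found ineligible stay in. For safety, the answer is yes by rule, because the per-protocol set requires adherence on eligibility.

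**Step 4: how much could removal matter?** This is an illustration on assumed inputs. The planned total of 115 comes from 'Sample size'. The following are assumptions:

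- 1:1 allocation, giving arms of 58 (7 days) and 57 (14 days)
- equal true 90-day mortality *m*
- the numbers removed, *r7* and *r14*
- the share *f* of removed patients who died

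The article does not list which outcomes count as safety outcomes. The figures therefore apply to mortality only where it is analysed in a set that drops these patients.

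Shift = (58*m* − *f*·*r7*)/(58 − *r7*) − (57*m* − *f*·*r14*)/(57 − *r14*)

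At *m* = 25% the expected deaths are 14.5 and 14.25. With *r7* = 1, *r14* = 0 and *f* = 1: 13.5/57 − 14.25/57 = 23.7% − 25.0% = −1.3 points. With *r7* = 3: 11.5/55 − 25.0% = 20.9% − 25.0% = −4.1 points.

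| Removed (7-day / 14-day) | All removed had died | Half had died |
|---|---|---|
| 1 / 0 | −1.3 | −0.4 |
| 2 / 0 | −2.7 | −0.9 |
| 3 / 0 | −4.1 | −1.4 |
| 3 / 1 | −2.8 | −0.9 |
| 5 / 1 | −5.7 | −1.9 |

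Negative values favour 7 days. Over *m* from 15% to 35% and the same scenarios, the shift runs from −0.3 to −6.5 points. If nobody leaves the analysis and vital status is known, it is 0.

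**The case against.** The strongest reply is that withdrawal is not removal. The same section promises follow-up of all consented patients and intention-to-treat for the primary analyses, and 'Frequency of analyses' repeats it. This stands. A reader might infer that late failures will be deleted from the mortality comparison, but the documents do not say that.

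A second reply is that a focus found only after relapse was neither suspected nor documented before randomization, so it does not meet the exclusion as worded. That is a fair reading of the criterion. The text does not say that eligibility is to be judged in that way, however, and the physician ground does not depend on the criterion at all.

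A third is that the permission sentence follows one about consent withdrawal and probably belongs to it. This is plausible, and a clearer sentence would settle it.

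A fourth is that cut-offs and blinded eligibility rulings are often left to the full protocol or analysis plan, which are not shown. That limits how far their absence alone can be pressed. But the article itself fixes the withdrawal grounds and the per-protocol rule for safety, and those two together create the problem.

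Two further inferences are tempting. One is that losses would fall mainly on the 7-day arm. This is plausible, because worsening after antibiotics stop prompts a search for a focus, but the documents neither state nor quantify it. The other is that withdrawals would lift adherence and so help the decision to proceed. That does not follow from this mechanism. A course stopped at day 7 lies inside the 7 ± 2 day window and counts as adherent, unless later retreatment were counted as the same course, which the article does not say.

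**Conclusion.** The point holds in a limited form. Patients can be withdrawn as ineligible or at a physician's discretion after the assignment is known, without an evidence cut-off or blinded ruling, and the wording leaves open whether their data continue without new permission. For the intention-to-treat analyses this is a risk to be closed by clarification. For the per-protocol safety analysis it is a stated rule that can lose late-detected failures through arm-aware judgement.

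The size cannot be taken from the documents. The illustrative range of 0.3 to 6.5 points rests on assumed mortality, assumed numbers removed and an assumed imbalance between arms. The decision on feasibility rests on recruitment and adherence, so it is not shown to be biased. What is exposed is the safety reading of the pilot, and the main trial if pilot patients are carried into it.

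**What to change.** Reword 'Withdrawal from study' and the per-protocol definition as follows:

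1. Only withdrawal of consent, or a duplicate randomization, ends data collection.
2. Patients found ineligible after randomization, or taken off the assigned duration by a physician, remain in follow-up to day 90 under their existing consent. They stay in the intention-to-treat and adherence denominators. This concerns data only and leaves treatment decisions where they are.
3. Any exclusion from the per-protocol safety set for ineligibility rests only on information available before the day-7 release, and is judged by assessors blinded to the arm. Evidence up to that point cannot depend on the assignment, so such exclusions should not differ systematically between arms.
4. Safety outcomes are reported by intention-to-treat alongside the per-protocol analysis.

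The cost is small: a rewording, a matching change to the withdrawal form, and one extra set of safety tables. The 90-day contact is already planned, and the blinded committees already foreseen for outcomes could take on the eligibility rulings. The reported figures may be slightly less favourable.

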### Protocol violation

A protocol violation form will be completed in case of the following violations:Adequate antibiotic treatment stopped by treating physician before RCT-dictated antibiotic stop dateAdequate antibiotic treatment continued by treating physician after RCT-dictated antibiotic stop date

We will also document the reason for protocol violation, responsible person for protocol violation (for example, attending physician, trainee physician, nurse, pharmacist, *etcetera*) and if there were any clinical explanations that might have resulted in the protocol violation.

### Frequency and duration of follow-up

The antibiotic treatment durations may extend beyond ICU discharge for some patients, and beyond hospital discharge for a minority. Our retrospective observational study showed that 27% of patients were discharged from ICU to hospital wards on or before day 7 of adequate antibiotic treatment and 4% were discharged from hospital before day 7. Patients will be reviewed daily in ICU, at hospital discharge and at 90 days post-randomization. If a patient is discharged from hospital prior to 90 days post-randomization, the research coordinator will contact the patient (or substitute decision-maker as appropriate) by telephone to determine their disposition and vital status.

### Study drug related daily data

The research coordinator will assess the patient daily (each morning) for 14 days after randomization to ensure the clinical team adheres to the study treatment duration protocol. If the clinical team proposes stopping antibiotics prior to the assigned stop date, the research coordinator and/or site investigator will follow-up with the clinical team to continue appropriate antibiotics; if the team extends antibiotics beyond the assigned stop date the research coordinator will suggest discontinuing the antibiotics.

### Primary and secondary outcome measures

The primary outcome for the main BALANCE trial is 90-day mortality and the primary outcome for the pilot trial is feasibility as defined by: (a) adherence to treatment duration protocol (proportion of treatment courses); and (b) rate of recruitment (patients per site, per month). We will consider the main trial to be feasible and worthy of embarking on a larger mortality-powered non-inferiority RCT if 90% of antibiotic treatment courses are within 7 ± 2 days in the shorter duration treatment arm or 14 ± 2 days in the longer duration treatment arm; and, if we achieve recruitment rates of at least 1 patient per 4 weeks, on average, per participating site. Secondary outcomes include ICU, hospital and 90-day mortality rates, relapse rates of bacteremia, antibiotic allergy and adverse events, rates of *Clostridium difficile* infection in hospital, rates of secondary infection or colonization with antimicrobial resistant organisms, ICU and hospital lengths of stay, mechanical ventilation duration, vasopressor duration in ICU and decline in procalcitonin levels.

### Statistical analysis

#### Sample size

To estimate our expected adherence rate of 90% within a margin of error of ± 5% (that is, actual adherence 85 to 95%), with 95% confidence, we plan to enroll 115 patients. At our expected recruitment rate of 1 patient/site month across 15 sites, we will need approximately 10 to 24 months to recruit these 115 patients given variability in site trial start-up steps (REB approval, data sharing agreements and contracts). By the time we have recruited 115 patients, we will know with 95% confidence that this number of sites would be able to recruit 95 to 138 patients over the same time interval in a future trial; this data will then be used to estimate the number of centers needed for the main trial (see Additional file 1 for detailed sample size calculation).

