### Setting

To maximize efficiency, the BALANCE pilot trial will aim to involve a geographically and clinically diverse spectrum of ICUs across Canada. The study will be initiated in October 2014 at Sunnybrook Health Sciences Centre (SHSC) in Toronto, Ontario, and then rolled out to additional sites, starting with Kingston General Hospital in Kingston, Ontario. These two sites will be sufficient to accrue the intended pilot sample size of 115 patients, but we aim to roll out to 13 additional sites, if sufficient funding is acquired, to improve external generalizability of the pilot trial findings. See Additional file 1 for participating pilot sites.

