### Analysis of primary outcomes

The primary outcomes will be analyzed as follows:(i).*Rate of recruitment*: We will consider the main trial to be feasible if we achieve recruitment rates of at least 1 patient per month per participating site. We will report recruitment rates with 95% confidence intervals.(ii).*Adherence to treatment duration protocol*: We will consider the main trial to be feasible if 90% of antibiotic treatment courses are 7 ± 2 days in the shorter duration treatment arm, and at least 90% of antibiotic treatment courses are 14 ± 2 days in the longer duration treatment arm. We will report proportion of adherence with 95% confidence intervals.

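### The stated ±5% margin on 90% adherence needs 139 patients; 115 give about ±5.5 points overall, and about ±7.8 points per arm if the 90% threshold is judged by arm

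*Protocol article*

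**What the plan says.** The Sample size section gives the target as "To estimate our expected adherence rate of 90% within a margin of error of ± 5" percent, and spells this out together with the sample size: "actual adherence 85 to 95%), with 95% confidence, we plan to enroll 115 patients". The Setting section confirms that this is the whole trial: "the intended pilot sample size of 115 patients". The same Sample size section also states a precision for recruitment, 95 to 138 patients over the same interval, and refers to Additional file 1 (not shown) for the detailed calculation.

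Adherence is one of the two primary feasibility outcomes, and its criterion is worded in three ways:

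- The Abstract gives a single figure, adherence of 90% or more.
- Primary and secondary outcome measures requires 90% of courses to lie within two days of the assigned duration, with the two arms joined by *or*. This can be read as one pooled proportion.
- Analysis of primary outcomes, item (ii), requires 90% in the 7-day arm "and at least 90% of antibiotic treatment courses are 14" days, give or take two, in the longer arm. That is a threshold in each arm. It adds: "We will report proportion of adherence with 95% confidence intervals".

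**The concern.** All the inputs to the adherence calculation are printed, and they do not lead to the printed sample size. A reader who relies on the sentence will expect a tighter interval than the pilot can report.

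The second issue matters more. The stated margin belongs to a single proportion estimated from all 115 patients. If feasibility is judged in each arm, each of the two proportions that decide it rests on about half the patients, and no precision is stated for them. Whether the main trial is called feasible depends partly on these proportions, so the stated precision should describe the quantity that is judged.

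**Working it through.** **Inputs.** Expected adherence p = 0.90, margin d = 0.05, 95% confidence taken as two-sided (z = 1.96) because the margin is given as ±, and N = 115 in total (Sample size; Setting). There are two arms (Trial interventions). The allocation ratio is not stated; 1:1 is assumed, giving 57 or 58 per arm. Loss to follow-up is described as negligible, so no inflation applies.

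**Step 1: try to reproduce 115.** For a single proportion, n = z²p(1 − p)/d² = 1.96² × 0.9 × 0.1 / 0.05² = 138.3, so 139. This does not match 115. The difference is 24 patients, or 24/139 = 17%.

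**Step 2: try other methods.** Sample size for ±5 points at 90%:

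| Method | n |
|---|---|
| Wald, z = 2 | 144 |
| Wilson | 141 |
| Exact (Clopper-Pearson) half-width | 158 |
| Arcsine, lower / upper limit | 166 / 104 |
| Wald, 90% confidence | 98 |

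None gives 115. A finite-population correction gives it only for a population of about 678, which the article does not mention.

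**Step 3: precision from 115.** Half-width = z√(p(1 − p)/n) = 1.96 × √(0.09/115) = 0.0548. The interval is 84.5% to 95.5%. Wilson gives a half-width of 5.55 points.

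**Step 4: rounding.** For ±5.5 points, n = 1.96² × 0.09 / 0.055² = 114.3, so 115. Thus 115 is the smallest sample whose Wald half-width falls below 5.5 points (114 gives 5.507; 115 gives 5.483). In whole percent, 84.5% to 95.5% prints as 85% to 95%.

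**Step 5: precision per arm.**

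- n = 57: 1.96 × √(0.09/57) = 0.0779
- n = 58: 1.96 × √(0.09/58) = 0.0772

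The half-width is about 7.7 to 7.8 points, an interval of about 82% to 98%. To hold ±5 points in each arm would take about 2 × 139 = 278 patients.

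**Step 6: does the reading of the criterion matter?** Suppose true adherence is exactly 90% in both arms and the arms are independent.

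- Pooled reading: the probability that the observed proportion reaches 90% (at least 104 of 115) is about 0.52.
- Arm-by-arm reading: at least 52 of 57 has probability 0.489 and at least 53 of 58 has probability 0.471. Both together: 0.489 × 0.471 = 0.23.

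**Step 7: the other precision statement.** The exact Poisson 95% interval for a count of 115 is 94.9 to 138.0, which reproduces the printed 95 to 138.

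**The case against.** The strongest reply is that the article prints whole percents, and in whole percents its figures hold: 5.48 becomes 5, and 84.5% to 95.5% becomes 85% to 95%. Since 115 is exactly the smallest sample for which this is so, rounding is a plausible origin, and the recruitment interval in the same section is also printed in whole numbers. The practical effect on the pooled estimate is slight. If true adherence is 90%, the exact probability that 115 patients give an estimate within 5 points is 94.0%. The feasibility rule compares the observed proportion with 90% and uses no confidence limit, so half a point of precision changes no decision. All of this stands, and it limits the pooled part of the point to wording. Additional file 1 may also state the method or the rounding.

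On the per-arm figure, the Sample size section speaks of one adherence rate and the total sample, and claims no precision by arm. That also stands: ±7.8 points does not show that the sentence is false. It shows that, under the criterion in Analysis of primary outcomes, the sentence describes a different proportion from the ones judged. Rounding cannot close that gap.

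A reader might go further and infer that the pilot's only justification for its size fails. The documents do not support this, because the recruitment interval also appears there and reproduces. Nor do they support the inference that the pilot must grow to 139 or 278, since nothing in the feasibility rule depends on attaining ±5 points.

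**Conclusion.** The point holds in limited form. Taken literally, 90% ± 5 points with 95% confidence needs 139 patients; 115 give about ±5.5 points, a shortfall of about half a point that rounding may account for. If the threshold is applied by arm, the relevant precision is about ±7.8 points, more than half as wide again as the printed margin. That figure rests on an assumed 1:1 allocation and on the wording in Analysis of primary outcomes. The Abstract and Primary and secondary outcome measures can be read as a pooled rule, so it cannot be said that the arm-level figure is the governing one. What can be said is that the criterion is not fixed consistently and the stated precision fits only one reading of it. Severity is minor to moderate.

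**What to change.** Keep 115 patients and make two text changes.

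1. In Sample size, restate the precision, for example: *With 115 patients, an expected adherence of 90% is estimated to within about ±5.5 percentage points overall (95% confidence).* If the threshold is applied by arm, add: *and to within about ±7.8 percentage points in each arm, assuming equal allocation.*
2. Reconcile the adherence criterion in Primary and secondary outcome measures with that in Analysis of primary outcomes, and align the Abstract, so that it is clear whether one pooled proportion or two arm-specific proportions must reach 90%. The precision quoted should be that of the proportion judged.

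The choice of interval method can stay with the trial team. The cost is one sentence on precision and one consistent wording of the criterion. No patients are added, and the stated precision becomes somewhat less favourable.

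### The 95-to-138 recruitment forecast is a confidence interval for the expected count, so as a 95% statement about patients recruited in a future trial it is too narrow

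*Protocol article*

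**What the plan says.** The Sample size section of the protocol article fixes the pilot at 115 patients and then says what that count will reveal about recruitment. "By the time we have recruited 115 patients", it states, "we will know with 95% confidence that this number of sites would be able to recruit 95 to 138 patients". The horizon of this forecast is given as "over the same time interval in a future trial". The next clause gives the purpose: "this data will then be used to estimate the number of centers needed for the main trial".

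The same section assumes one patient per site per month at 15 sites and allows 10 to 24 months for accrual "given variability in site trial start-up steps". It names no count distribution and gives no figure for how far site rates differ. The detail is deferred ("see Additional file 1 for detailed sample size calculation"), and that file is not at hand.

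Under Analysis of primary outcomes, the planned inference for recruitment is an interval for the rate: "We will report recruitment rates with 95% confidence intervals".

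**The concern.** The sentence attaches 95% confidence to a number of patients, for a given number of sites and length of time, in a trial that has not yet happened. That is a forecast of a future count, and it has two sources of error. The pilot estimates the underlying rate imprecisely, and the future count will scatter around whatever that rate is. A confidence interval for the mean covers only the first. If 95 to 138 is such an interval, it is too narrow for what the sentence says.

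The lower end matters most for planning. Someone who takes 95 as a floor with a 2.5% chance of falling below it would think accrual safer than the data support.

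**Working it through.** **Inputs.** From the Sample size section: observed count x = 115; confidence level 95%; stated limits 95 and 138; same number of sites and same time in the future trial, so an exposure ratio of 1:1. Assumed: recruitment counts are Poisson and site rates do not change. The article states neither.

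**Step 1: reproduce the stated figure.** The exact Poisson 95% confidence interval for the mean given x events is

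- lower = χ²(0.025; 2x)/2 = χ²(0.025; 230)/2 = 94.94
- upper = χ²(0.975; 2x + 2)/2 = χ²(0.975; 232)/2 = 138.04

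This rounds to 95 and 138. The alternatives come close, but none rounds to both limits:

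| Interval for the mean | Limits |
|---|---|
| Exact Poisson | 94.9 to 138.0 |
| Wald, 115 ± 1.96√115 | 94.0 to 136.0 |
| Square root | 94.9 to 137.0 |
| Score | 95.8 to 138.0 |
| Log | 95.8 to 138.1 |
| Gamma, recruiting until 115 | 94.9 to 136.9 |

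The match supports the Poisson assumption and identifies the quantity as an interval for the expected count.

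**Step 2: prediction interval for the future count Y at equal exposure.** If X and Y share one Poisson mean, Y given X + Y is binomial with probability 0.5. Keeping every y that a two-sided 5% test does not reject against x = 115 gives **87 to 147**. The tail probability is 0.0286 at y = 87 (kept) and 0.0240 at y = 86 (rejected). At the top it is 0.0276 at y = 147 (kept) and 0.0241 at y = 148 (rejected).

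Other forms agree:

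- negative binomial: 87 to 146 or 87 to 147, depending on the size parameter (115 or 115.5)
- square root, (√115 ± 1.96√0.5)²: 87.2 to 146.6
- Wald, 115 ± 1.96√(2 × 115): 85.3 to 144.7, the crudest of the set

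The width is 147 − 87 = 60, against 138 − 95 = 43 as stated. That is a ratio of 60/43 = 1.40. The lower limit moves by 95 − 87 = 8 patients.

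**Step 3: what the stated interval achieves as a forecast.** With X and Y independent Poisson with mean 115, the exact confidence interval computed from X contains Y with probability 0.844 (0.853 if its limits are rounded to whole patients). Conditioning on 115 observed, the negative binomial predictive probability of 95 to 138 is 0.85. The predictive probability of fewer than 95 is 0.074 to 0.083 for size parameters from 116 down to 115, so about 7 to 8%, where a 95% interval implies 2.5%.

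**Step 4: how much this matters for a larger trial.** If the future exposure is k times the pilot's, the approximate relative half-width of a forecast is 1.96√((1 + 1/k)/115).

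- k = 1: 1.96√(2/115) = 25.8%
- k = 10 (assumed; the article gives no main-trial size): 1.96√(1.1/115) = 19.2%
- confidence interval for the rate alone: 1.96√(1/115) = 18.3%

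The gap is clear at equal exposure, which is the case the sentence describes, and nearly vanishes when the future trial is much larger.

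**The case against.** The best defence is that the wording about what the sites would be able to recruit describes capacity, meaning the expected number. For that quantity the interval is correct, and it agrees with the plan to report confidence intervals for the rate. This reading is possible, but it sits badly with a sentence that names a patient count, a period and a future trial. If it is what was meant, the sentence only needs to say expected number.

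The unseen Additional file 1 may explain the method. It could not turn these limits into a 95% prediction interval under the Poisson model that reproduces them.

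Three further points stand and limit the finding:

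- **Nothing is miscalculated.** A reader might infer an arithmetic error. The limits are right for the expected count; the description is what goes wrong.
- **The interval is not said to set the number of centers.** A reader might infer that it does. The text says only that the data will be used for this, and the pilot's actual rate and interval will replace the hypothetical one. As Step 4 shows, the rate's own interval is close to sufficient for a much larger trial under the same model.
- **Variation between sites cannot be quantified from the article.** A reader might want a much wider interval on this ground. The variation would widen a forecast for new sites, but no variance is given. Pilot sites may also continue, because the Trial status section foresees rolling pilot patients into the main trial if no substantive protocol change is needed. Any width based on an assumed coefficient of variation would be illustrative only.

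**Conclusion.** The sentence is wrong as written. The interval it gives does not have 95% confidence for a future count: coverage is about 85%, and the corresponding 95% prediction interval is about 87 to 147. This rests on Poisson recruitment, inferred from the match in Step 1, and on the same sites recruiting at unchanged rates over the same active time.

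The consequence is modest. The feasibility thresholds for recruitment and adherence do not use this interval, so the pilot's go-ahead decision is untouched. The article does not support a conclusion that main-trial planning is compromised; it supports only that one planning statement is more confident than its own figure allows.

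**What to change.** Reword the sentence in the Sample size section along these lines: *the 95% CI for the expected number is 95 to 138; the 95% prediction interval for the number recruited by the same sites over the same active time is about 87 to 147, assuming Poisson recruitment and unchanged site rates.* A short remark that differences between sites would widen this further is worth adding, without a figure.

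The cost is one sentence and a slightly less favourable forecast. Sample size, conduct and feasibility criteria stay as they are. A site-level recruitment model for planning the main trial would be a reasonable choice, but the correction does not require it.
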